## OBJECTIVES

To describe the protocol of an educational intervention using digital technology for family caregivers of older adults who are stroke survivors to develop home care skills.

## METHODS

This is a randomized, blinded, pragmatic trial (PT) with three-month follow-up after hospital discharge, called “Digital educational intervention for family caregivers of older adults after stroke (e-SHARE)”. All stages are in accordance with CONsolidate Standards Of Reporting Trials (CONSORT) extension for PT recommendations. The protocol is based on the Standard Protocol Items: Recommendations for Interventional Trials (SPIRIT 2013 Statement).

### Study location

The study is being developed in the emergency service, in the clinical inpatient units and in the Special Care Unit - Stroke of a university hospital, a reference for the care of stroke patients in the city of Porto Alegre, Rio Grande do Sul, Brazil.

### Eligibility criteria

Study participants are family caregivers of older adults selected at hospital admission who play the role of primary care provider. Family caregivers of older adults will be excluded from the study if: (a) they live in a long-term care facility; (b) they do not have access to the internet and a device to access it, or are not able to use them, as verified through a digital aptitude checklist developed for the study; (c) they do not have a telephone line for contact; (d) they are accompanying older adults who died during the participant recruitment phase.

### Intervention

The educational intervention will be carried out by two nurses, through an online course in the format of Massive Open and Online Courses (MOOCs). MOOCs are teaching tools that provide flexible hours, quality material and low cost for implementation^(5)^.

The MOOC for family caregivers was developed digitally and made available on the Moodle Platform, since this platform provides access statistics. During the study period, access will be restricted to IG members. MOOC development is based on the Manual for Caregivers of Older Adults with Stroke^(6)^. The MOOC includes 12 modules, which can be accessed as many times as necessary by caregivers, in random order, according to older adults’ and caregivers’ care needs. Telephone contacts will also be made with IG participants seven days, 30 days, 60 days and 80 days after hospital discharge and a hotline will be made available for contact.

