**Methods::**

randomized pragmatic trial protocol. Fifty-eight family caregivers will be recruited and randomized into two groups. The intervention will consist of a virtual educational action, in addition to telephone contacts at seven, 30, 60 and 80 days after discharge. The control group will not receive the intervention. Primary outcomes will be caregivers’ ability to care, knowledge and performance. Secondary outcomes will be caregiver burden and older adults’ functional capacity. Outcomes will be assessed at the time of participant recruitment and three months after discharge.

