**Figure 1 f1:**
[figure not shown]
Graphical representation of study logistics diagram and operationalization of data collection, Porto Alegre, Rio Grande do Sul, Brazil, 2024

The study will begin with the identification of patients aged 60 or older who have a medical diagnosis of stroke during their current hospitalization. The older adults selected will receive a visit from the researchers to verify the existence of a family caregiver and to assess whether the caregiver and the older adult meet the inclusion criteria. Baseline data will be collected for those who agree to participate. After allocation, those included in the IG will receive an instructional visit from the intervention nurses close to discharge. The purpose of the visit is to provide detailed guidance on the intervention.

Caregivers will be contacted by telephone three months after discharge to conduct the final assessment. Data collection will be done via online conference. The three-month interval meets Brazilian reproducibility study of the Scale of Informal Caregiver Capabilities for Older Adults Dependent on Stroke (ECCIID-AVC) recommendations, which will be used in the study^(7)^.

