### Sample size

Sample size was calculated, considering a power of 80%, a significance level of 5% and a Cohen’s effect size of 0.8, adding 10% for possible losses and refusals, totaling 58 participants, divided equally into IG and CG.

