### Statistical methods

For data analysis, the intention-to-treat technique will be used. The difference between baseline and final scores will be assessed by paired Student’s t-test, with a 95% Confidence Interval. A p<0.05 value will be considered significant. For simultaneous intraand intergroup comparisons, the Generalized Estimating Equations model with Bonferroni adjustment will be used.

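### Only the intervention arm is described as being in contact with the study between discharge and the final assessment, so loss may differ by arm, and the planned GEE protects the between-group comparison only under assumptions about that loss

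*Protocol article*

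**What the plan says.** In the protocol article, the Intervention section states: "Telephone contacts will also be made with IG participants seven days, 30 days, 60 days and 80 days after hospital discharge". The same sentence adds that "a hotline will be made available for contact". The Abstract says of controls: "The control group will not receive the intervention". No study contact with controls is described between discharge and the end of follow-up. At that point the Participant timeline makes no distinction by arm: "Caregivers will be contacted by telephone three months after discharge to conduct the final assessment". The final data are then collected by online conference.

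Eligibility criteria exclude caregivers in either arm if "they do not have a telephone line for contact". Sample size makes one allowance for both arms: "adding 10% for possible losses and refusals, totaling 58 participants, divided equally into IG and CG". Statistical methods names intention-to-treat, a paired t-test from baseline to final score and, for comparisons within and between groups, "the Generalized Estimating Equations model with Bonferroni adjustment will be used". Study limitations foresees loss because the patient dies or enters institutional care, or because someone else takes over the caring.

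**The concern.** Four calls, the last about ten days before a three-month assessment, keep telephone numbers current and the caregiver engaged. As described, controls have no such thread. What is tested as treatment may therefore also act as a retention procedure in one arm.

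If loss differs by arm and is also related to the scores, the caregivers with a final score no longer represent the two randomised groups in the same way. The between-group contrast then mixes effect with selection, on all three primary outcomes and on burden. Analysing caregivers as randomised does not supply final scores that were never collected. Without weighting, a GEE is in general valid only if loss is unrelated to the scores; beyond that, its validity depends on the working correlation and on why caregivers are lost.

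**Working it through.** **1. The plan's own figure.** Inputs from Sample size: "considering a power of 80%, a significance level of 5% and a Cohen’s effect size of 0.8". Sidedness is not given; two-sided is assumed. The two-sample t-test (noncentral t) needs 25.52, so 26 per arm, 52 in total. With the 10% allowance, 52/0.9 = 57.8 and 52 × 1.1 = 57.2; both round up to 58, or 29 per arm. The stated figure reproduces.

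**2. Is it a power problem?** Power at an effect size of 0.8, by numbers analysed:

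| Analysed (arm + arm) | Power | Same total, balanced | Power |
|---|---|---|---|
| 28 + 24 | 80.5% | 26 + 26 | 80.7% |
| 28 + 22 | 78.6% | 25 + 25 | 79.1% |
| 28 + 20 | 76.3% | 24 + 24 | 77.4% |

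The imbalance costs about one percentage point or less; the rest of each drop is total loss. Power is not the issue.

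**3. Bias if loss depends on the baseline score.** The article gives no loss by arm, no SDs and no correlation, so these are assumptions: no true effect; baseline SD 1; baseline–final correlation r from 0.5 to 0.7; final SD k = 1 or 1.5; log-odds of loss rising by 1.5 for each SD of lower baseline score; loss of 5% in the intervention arm and 20% or 30% in controls.

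Let m be the mean baseline score of caregivers who complete. Integrating over the normal distribution gives m = 0.065 at 5% loss, 0.227 at 20% and 0.327 at 30%. Let D be m in the intervention arm minus m in controls:

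- 5% vs 20%: D = 0.065 - 0.227 = -0.162
- 5% vs 30%: D = 0.065 - 0.327 = -0.262
- equal loss: D = 0

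Completers' expected final score is r·k·m. For the group-by-time contrast with two visits:

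- **Independence GEE:** bias = r·k·D. With k = 1, the smallest is 0.5 × (-0.162) = -0.08 and the largest is 0.7 × (-0.262) = -0.18 SD.
- **Exchangeable GEE:** bias = (r·k - w)·D, where w is the fitted working correlation. With k = 1, w is close to r (0.455 for r = 0.5; 0.648 for r = 0.7), so the bias is (0.5 - 0.455) × (-0.162) = -0.007 to (0.7 - 0.648) × (-0.262) = -0.014, about 0. With k = 1.5, one common variance is the wrong scale: (0.75 - 0.430) × (-0.162) = -0.05 to (1.05 - 0.621) × (-0.262) = -0.11, in baseline SDs.
- **Likelihood model, unstructured covariance:** the fitted slope estimates r·k itself, so the bias is about 0 for either k.

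Equal loss gives D = 0 and no bias in any row. A large simulation (1,000,000 per arm) agreed with these figures. The negative sign means the intervention looks worse, because controls who score low drop out and raise the control mean. If the intervention arm lost more, the sign would reverse.

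**4. Other loss mechanisms.** Loss unrelated to scores gave bias of about 0 for every method, even when unequal. If loss depends on the unseen final score (5% vs 20–30%, r = 0.5, equal SDs, slope 1 to 2), the same simulation gave about -0.13 to -0.30 SD for independence GEE and still about -0.10 to -0.24 SD for the likelihood model.

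**The case against.** The calls and hotline are the treatment under test in a pragmatic trial, and controls by design do not receive it. Nothing here is misstated or contradictory. That stands, and the calls should not be touched.

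A reader might infer that controls will be lost more often. The article does not support this. It reports no loss by arm, requires a telephone line in both, and describes the same final call for all. A course of 12 modules plus four calls could equally raise loss in the intervention arm. Moreover, the reasons for loss that the article lists are not obviously altered by calls, while caregivers who merely become unreachable are not shown to differ in score. A partial answer is that the trial's own hypothesis is lower burden, and a change of caregiver or institutional care may follow burden. That is plausible, not established.

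A reader might also infer that the named analyses leave the comparison unprotected. That goes too far. The GEE makes the between-group comparison, uses all available scores, and with an exchangeable correlation and equal SDs is nearly unbiased under baseline-dependent loss. The paired t-test is a baseline-to-final comparison, so its restriction to complete pairs is no flaw in the between-group analysis. The working correlation and missing-data rules may sit in a fuller document; their absence from an article is not held against it.

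**Conclusion.** The point holds as a risk with a cheap remedy, not as an error. The contact asymmetry is in the text; unequal loss is an inference from it, in either direction. With assumed loss of 5% vs 20–30% depending on baseline score, the bias in the GEE contrast runs from about 0 to about -0.18 SD with equal SDs, according to the working correlation. It is about -0.05 to -0.11 SD under exchangeable if the final SD is 1.5 times larger. Against the planned effect size of 0.8 these are modest shifts, though large enough to cloud a smaller effect. They rest on assumed loss rates, correlation, SDs and strength of selection, and vanish if loss is equal in the two arms under the same mechanism, or unrelated to scores.

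**What to change.** 1. **Conduct.** Leave the nurse calls as they are. Record a second contact person at baseline, and send both arms the same automated message confirming contact details and the final appointment. It should carry no teaching and come from neither the intervention nurses nor the blinded assessors. The small downside is that it reminds controls they are in a study. It will not prevent loss through death or institutional care.
2. **Statistical methods.** Make the between-group analysis a likelihood-based linear mixed model with baseline and final score as responses, unstructured covariance and all 58 randomised caregivers. This is valid when loss is explained by observed scores. Report loss and its reasons by arm.
3. **Sensitivity analysis.** No such model corrects for loss that depends on the unseen final score. Vary the assumed outcomes of lost caregivers in both arms, controls included, and show how far they must move before the conclusion changes.

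The cost is a few automated messages, one extra baseline item and a few sentences of analysis text, with no added staff, visits or participants.

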### Results

The intervention aims to equip family caregivers to assist older adults in ADLs after hospital discharge.

### Participant timeline

Figure 1 presents the study logistics diagram.

**Figure 1 f1:**
[figure not shown]
Graphical representation of study logistics diagram and operationalization of data collection, Porto Alegre, Rio Grande do Sul, Brazil, 2024

The study will begin with the identification of patients aged 60 or older who have a medical diagnosis of stroke during their current hospitalization. The older adults selected will receive a visit from the researchers to verify the existence of a family caregiver and to assess whether the caregiver and the older adult meet the inclusion criteria. Baseline data will be collected for those who agree to participate. After allocation, those included in the IG will receive an instructional visit from the intervention nurses close to discharge. The purpose of the visit is to provide detailed guidance on the intervention.

Caregivers will be contacted by telephone three months after discharge to conduct the final assessment. Data collection will be done via online conference. The three-month interval meets Brazilian reproducibility study of the Scale of Informal Caregiver Capabilities for Older Adults Dependent on Stroke (ECCIID-AVC) recommendations, which will be used in the study^(7)^.

### Sample size

Sample size was calculated, considering a power of 80%, a significance level of 5% and a Cohen’s effect size of 0.8, adding 10% for possible losses and refusals, totaling 58 participants, divided equally into IG and CG.

### Recruitment

Participants will be recruited through daily consultation of the hospital’s computerized system.

### Allocation

After the instruments are applied, participants will be randomized to either the CG or IG group. To do this, a list generated by the website randomizer.org will be used. A professional external to the research group will be responsible for the list.

### Blinding

Researchers who will perform the initial and final assessment of participants will be blind to allocation.

### Data collection

Data collection will be performed at baseline and three months later. A structured questionnaire was developed with sociodemographic and clinical information from family caregivers and older adults. All information regarding older adults will be provided by caregivers. Instruments that assess caregivers’ ability to care, ECCIID-AVC, their knowledge and performance in caring for older adults (Nursing Outcomes Classification (NOC)) as well as instruments that assess the burden of these caregivers (Caregiver Bunder Scale (CBS)) and the measure of functional independence of older adults (Functional Independence Measure (FIM)) will also be applied.

Regarding the instruments used in the study, the ECCIID-AVC assesses the different capabilities that family caregivers have or need to improve when providing care to dependent older adults after a stroke. In the reproducibility study of the Brazilian version, the ECCIID-AVC showed satisfactory test-retest reliability (Intraclass Correlation Coefficient = 0.94; 95% Confidence Interval = 0.91-0.96) and excellent internal consistency reliability (Cronbach’s alpha = 0.914)^(7)^.

The NOC is a standardized taxonomy for nursing-sensitive outcomes intended for clinical practice and with the objective of verifying changes in the condition of a patient, family or community after an applied nursing intervention^(8)^. For the present study, the outcomes “Knowledge: Stroke Management” and “Caregiver Performance: Direct Care” were selected. A group of ten experts with knowledge and experience in using this classification assisted the researchers in selecting the indicators for these two outcomes. For each selected indicator, a conceptual definition and an operational definition were constructed.

Family caregivers’ burden will be assessed using the CBS. This scale was adapted and validated for the Brazilian context by Medeiros *et al*.^(9)^ with a population of caregivers of patients with rheumatic diseases. The intraand inter-observer reproducibility coefficients were 0.87 and 0.92, respectively, and the Portuguese version proved to be a valid instrument^(9)^.

Older adults’ functional capacity will be assessed using the FIM. The scale was translated into Brazilian Portuguese in 2000 and underwent validity for the Brazilian context in 2004. The Brazilian version of the scale has good cultural equivalence and good reproducibility^(10)^.

### Statistical methods

For data analysis, the intention-to-treat technique will be used. The difference between baseline and final scores will be assessed by paired Student’s t-test, with a 95% Confidence Interval. A p<0.05 value will be considered significant. For simultaneous intraand intergroup comparisons, the Generalized Estimating Equations model with Bonferroni adjustment will be used.

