In the local context, there is no evidence that an educational intervention based on skills development can improve caregivers’ ability, knowledge, and performance to provide care to older adults who have survived stroke. Thus, the present study considers the hypotheses that: (1) the educational intervention with digital technology, carried out by nurses for family caregivers of older adults with stroke sequelae, improves caregivers’ ability to care, performance, and knowledge in the intervention group (IG) when compared to caregivers in the control group (CG); (2) the intervention offered reduces caregiver burden; (3) older adults in the IG will present better functional capacity when compared to the CG.

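### A within-arm paired t-test held to p<0.05 stands beside the GEE model; it cannot test the between-arm hypotheses and should be made descriptive

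*Protocol article*

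**What the plan says.** The Statistical methods section of the protocol article names two analyses.

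- Within arm: "The difference between baseline and final scores will be assessed by paired Student’s t-test, with a 95% Confidence Interval". The next sentence is the decision rule: "A p<0.05 value will be considered significant".
- Within and between arms: "For simultaneous intraand intergroup comparisons, the Generalized Estimating Equations model with Bonferroni adjustment will be used".

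The hypotheses are at the end of the Introduction. Hypothesis 1 (ability to care, performance, knowledge) is stated as IG compared with CG. Hypothesis 3 is too: "older adults in the IG will present better functional capacity when compared to the CG". Hypothesis 2 reads only "the intervention offered reduces caregiver burden" and names no comparator.

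The Sample size section assumes "a power of 80%, a significance level of 5% and a Cohen’s effect size of 0.8, adding 10% for possible losses and refusals, totaling 58". The two arms are to be of equal size. According to Participant timeline and Data collection, baseline is taken during the stroke admission and the final assessment three months after discharge, by online conference.

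**The concern.** A paired t-test of baseline against final score asks whether the mean in one arm moved. It does not ask whether it moved more than in the other arm. Here movement in both arms is plausible without any intervention. Between the two assessments the older adult may recover function, the caregiver gains experience, and the setting changes from hospital to home. A paired test in the IG attributes all of this to the same mean change.

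Two misreadings are then open. One takes a significant change in the IG as an effect. The other takes significance in the IG but not in the CG as a difference between arms. Neither has a 5% error rate for the between-arm question. Hypothesis 2 is the most exposed, since its wording would not stop a reader from answering it with the IG change alone.

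The GEE sentence also puts within-arm and between-arm comparisons together under one Bonferroni adjustment. Within-arm comparisons that answer no hypothesis could therefore make the between-arm test stricter.

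**Working it through.** **1. Which test does the sample size belong to?** Inputs from Sample size: d = 0.8, power 80%, alpha 5% (two-sided assumed), 10% for losses.

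- Two-sample t-test (noncentral t): 25.52, so 26 per arm and 52 in total. With losses, 52/0.9 = 57.8 or 52 × 1.10 = 57.2; both round up to 58, or 29 per arm. The stated figure is reproduced.
- Paired t-test at d = 0.8: 14.3, so 15 pairs.

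The trial is sized for a comparison between arms, not for the paired test.

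**2. How often does the paired test mislead when the intervention does nothing?** The documents give no size for the change common to both arms, so it is assumed. Let δ be that change in SDs of the change score, and n = 26 pairs per arm (29 less losses). The paired statistic is noncentral t with n − 1 = 25 degrees of freedom and noncentrality δ√n, tested two-sided at 0.05. If p is the chance of significance in one arm, and the arms are independent with the same δ, the chance of IG significant and CG not is p(1 − p).

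| δ | δ√26 | p: IG paired test significant | p(1 − p): IG significant, CG not |
|---|---|---|---|
| 0.3 | 1.53 | 0.313 | 0.215 |
| 0.4 | 2.04 | 0.500 | 0.250 |
| 0.5 | 2.55 | 0.688 | 0.215 |
| 0.8 | 4.08 | 0.975 | 0.024 |

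The two misreadings behave differently. The first worsens steadily as the common change grows. The second peaks at 25% and falls away once both arms are nearly always significant.

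With all 29 per arm, p is 0.345, 0.548 and 0.739 at δ = 0.3, 0.4 and 0.5, and p(1 − p) is 0.226, 0.248 and 0.193.

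**3. Check by simulation, with a between-arm comparator.** There were 40,000 trials per setting and no intervention effect. The common change was 0.2 to 0.8 SD of the score and the baseline–final correlation 0.3 to 0.7, both assumed. With 26 per arm, the IG paired test showed significant improvement in 13% to 99.9% of trials. At 0.5 SD and correlation 0.5, where the SD of the change equals the SD of the score, it was 69%, matching the table. IG significant and CG not reached 25%, against about 2.5% when nothing changes. A two-sample test of the change scores stayed at 4.8% to 5.2% throughout.

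**4. What the replacement contrast gives.** Assume d = 0.8 in SDs of the final score, 26 per arm, and baseline–final correlation r. Baseline adjustment gives an effective size of 0.8/√(1 − r²). A comparison of change scores gives 0.8/√(2(1 − r)).

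| r | Adjusted: size, power | Change score: size, power |
|---|---|---|
| 0.3 | 0.839, 84% | 0.676, 67% |
| 0.5 | 0.924, 90% | 0.800, 81% |
| 0.7 | 1.120, 98% | 1.033, 95% |

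The baseline-adjusted contrast meets the planned 80% over this range with 58 randomised. The change-score contrast falls short at r = 0.3.

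**5. The Bonferroni family.** The article does not define it. As an illustration, two groups at two times give four means and 4 × 3/2 = 6 pairwise comparisons, so a per-comparison level of 0.05/6 = 0.0083. Two of the six are within-arm changes, and none is the baseline-adjusted difference between arms.

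**The case against.** The strongest reply is that the plan already contains a between-arm analysis. A reader who stops at the paired t-test might infer that it is the trial's test of effect, and that recovery and learning will be credited to the intervention. The article does not support that reading. It assigns the paired test to the baseline–final difference and never calls it the test of effectiveness. Two sentences later it names a GEE model for comparisons between groups. Such a model, with group, time and their interaction, can test hypotheses 1 and 3, and the sample size is that of a two-group comparison. False credit is a risk if the paired tests are used for inference, not a certainty. This part of the reply stands, and it lowers the severity.

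It is also fair that hypothesis 2, placed between two IG-versus-CG hypotheses in a randomised trial, is most naturally read as a comparison with the CG. The missing words are a small point of drafting.

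A third reply is that a condensed article may leave the primary contrast and the model terms to a full protocol or analysis plan that is not shown. That is right, and their absence is not the complaint. The complaint concerns what is stated: a within-arm significance test, followed directly by the p<0.05 rule, which fits neither the hypotheses nor the sample size. The GEE sentence does not cancel it. Since the GEE can also estimate within-arm change, the paired test adds only a second, uncontrolled route to a positive claim.

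**Conclusion.** The point holds at moderate severity. The plan names one analysis that can answer its hypotheses and one that cannot, and applies significance testing to the latter. If the paired test were used for inference, an ineffective intervention would show a significant IG change in 31% to 69% of trials, and significance in the IG alone in 21% to 25%. A between-arm test stays near 5%. These figures assume 26 pairs per arm, two-sided 5%, independent arms, and an equal change of 0.3 to 0.5 SD of the change score in both. The size of that change is not in the documents; recovery and caregiving experience make some change plausible but do not fix it. It does not follow that the trial lacks a between-arm analysis or that its conclusions will be wrong.

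**What to change.** In Statistical methods:

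- Drop the paired t-test as an inferential test. Report mean change in each arm descriptively, without a p-value.
- State that each hypothesis, including burden, is judged by one contrast: IG minus CG at three months, adjusted for baseline, with its 95% confidence interval and p-value. It can be estimated within the planned GEE.
- State that within-arm comparisons do not enter the Bonferroni family.

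In the Introduction, add *compared with the CG* to hypothesis 2.

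A GEE group-by-time contrast would also be a valid between-arm test. The baseline-adjusted form is preferred for its power at this sample size. The cost is a few sentences of wording, settled before the data are analysed. No new data are needed, and the sample size stays at 58.

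### The Bonferroni adjustment covers within- and between-group GEE comparisons together, while the trial is sized on one unadjusted 5% between-group test

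*Protocol article*

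**What the plan says.** All places are in the protocol article.

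- **Statistical methods.** Baseline-to-final differences are tested by paired t-test. Then: "For simultaneous intraand intergroup comparisons, the Generalized Estimating Equations model with Bonferroni adjustment will be used". The threshold is given as "A p<0.05 value will be considered significant". The GEE sentence is the only place in the section where a between-group test appears.
- **Sample size.** The calculation is described as "considering a power of 80%, a significance level of 5% and a Cohen’s effect size of 0.8", then "adding 10% for possible losses and refusals, totaling 58 participants", with equal groups. No allowance for multiple comparisons is mentioned.
- **Data collection.** "Data collection will be performed at baseline and three months later", so there are two time points.
- **Abstract, Methods.** "Primary outcomes will be caregivers’ ability to care, knowledge and performance", so there are three primary outcomes.
- **Introduction.** The main hypothesis is between-group: caregivers in the intervention group (IG) do better than those in the control group (CG) on those three outcomes.

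**The concern.** Two groups at two times give four cell means. The between-group comparison at three months, or the group-by-time term, addresses the main hypothesis. The within-arm changes do not, because they mix the effect of the intervention with whatever happens over three months after discharge. The baseline difference between groups does not either, because randomisation makes it null in expectation.

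If all these comparisons share one Bonferroni adjustment, the treatment comparison pays for tests that answer no stated hypothesis. The sample size makes no provision for this. In a trial of 58, the risk is missing an effect of the size the trial was designed to detect, with no gain in error control for the between-group hypothesis.

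**Working it through.** **Inputs.** d = 0.8, power 80%, alpha 5%, 10% losses, 1:1 allocation and a total of 58, all from Sample size. Two groups and two time points, from Sample size and Data collection. Assumptions: a two-sided test, and d applying directly to the contrast being tested. The article states neither.

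**Step 1: reproduce the plan's figure.** For a two-sample t-test with n per arm, the noncentrality is d × √(n/2) on 2n − 2 degrees of freedom.
- n = 25: noncentrality 0.8 × √12.5 = 2.828; power 79.2%, just short.
- n = 26: noncentrality 0.8 × √13 = 2.884, df = 50, critical t = 2.009; power 80.7%.
- Total 2 × 26 = 52. Then 52 / 0.9 = 57.8, or 52 × 1.1 = 57.2. Both round up to 58, or 29 per arm.

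A one-sided test needs only about 20 per arm (normal approximation) and does not give 58. The stated total therefore fits one unadjusted two-sided between-group comparison at 5%.

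**Step 2: possible families.** Four cells give four simple contrasts (two within-arm changes, two between-group differences) or six pairs in all. A family of two is a small case for reference. None of these counts is in the article.

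**Step 3: power when the treatment contrast is one of k comparisons.** Alpha is 0.05/k, with d = 0.8. The last two columns give what 80% power would need, the total being 2n / 0.9 rounded up.

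| k | alpha | critical t (df 50) | power, 26 per arm | power, 29 per arm (no losses) | evaluable n per arm for 80% | total with 10% losses |
|---|---|---|---|---|---|---|
| 1 | 0.0500 | 2.009 | 80.7% | 84.9% | 26 | 58 |
| 2 | 0.0250 | 2.311 | 71.6% | 76.9% | 31 | 69 |
| 4 | 0.0125 | 2.591 | 61.7% | 67.9% | 37 | 83 |
| 6 | 0.0083 | 2.747 | 55.8% | 62.3% | 40 | 89 |

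With equal arms, 69, 83 and 89 become 70, 84 and 90.

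**Step 4: sensitivity to baseline.** Suppose d = 0.8 is scaled on the raw-score SD and rho is the baseline/follow-up correlation. The effective d is then 0.8 / √(1 − rho²) for the baseline-adjusted three-month difference (df 49) and 0.8 / √(2(1 − rho)) for the difference in change. Power at 26 per arm:

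| rho | adjusted, alpha 0.05 | adjusted, alpha 0.0083 | change, alpha 0.05 | change, alpha 0.0083 |
|---|---|---|---|---|
| 0.3 | 84.2% | 60.9% | 66.7% | 38.8% |
| 0.5 | 90.4% | 71.7% | 80.7% | 55.8% |
| 0.6 | 94.2% | 79.9% | 88.5% | 68.2% |
| 0.7 | 97.7% | 89.5% | 95.5% | 83.0% |

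Baseline adjustment always helps. The difference in change helps only if rho exceeds 0.5. The article gives no rho.

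**Step 5: the three primary outcomes.** Bonferroni over three outcomes alone gives alpha 0.05/3 = 0.0167. Power at 26 per arm, without baseline adjustment, is 65.8%. For 80%, 35 evaluable per arm are needed: 70 / 0.9 = 77.8, so 78 in total.

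**The case against.** The strongest reply is that the GEE sentence does not define its family. It gives no number of comparisons and names no decisive contrast. It also fits a common practice in which the group-by-time term is tested once at 5% and Bonferroni applies only to the follow-up pairs. The p<0.05 threshold is stated without any reduction. On that reading power stays at 80.7%, if d = 0.8 refers to that contrast. This stands as a possible reading, but the article names no interaction test, so the reader has to supply it.

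Two further replies also stand in part. The six-pair family includes cross comparisons, such as IG at baseline against CG at three months, which are neither within- nor between-group in the ordinary sense, so 55.8% is the far end of a range. And a high baseline/follow-up correlation could offset the loss: at rho = 0.7 both models in Step 4 exceed 80% even with six comparisons. The sample size claims no such gain.

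It may also be said that a condensed article leaves the contrast list to the full protocol or analysis plan. That is fair for the missing count, and the count alone is not the point. The point is that the adjustment as stated and the alpha as stated do not match on their plain reading.

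A reader might infer two stronger claims. One is that the treatment comparison is certainly tested far below 5%, so that 80% power is not delivered. The text does not establish this, for the reasons above. The other is that multiplicity across the three primary outcomes is definitely left uncorrected. The article does not say what the Bonferroni adjustment spans beyond within- and between-group comparisons, so this too goes beyond the text.

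**Conclusion.** The point holds as a conditional mismatch between two stated rules. The sample size rests on one unadjusted 5% between-group test, while the analysis section puts between- and within-group comparisons under one Bonferroni adjustment and names no other between-group test. If the treatment contrast belongs to that family, power under the planning model is 71.6%, 61.7% or 55.8% for two, four or six comparisons. If it is tested once at 5%, power is 80.7%.

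These figures assume a two-sided two-sample t-test, d = 0.8 on the tested contrast, 26 evaluable per arm and no gain from baseline. The family sizes are inferred from the two-by-two layout. A planned GEE that uses baseline could do better, by an amount the article does not allow one to compute.

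**What to change.** In Statistical methods, name one IG–CG contrast per outcome as the decisive test: the three-month difference adjusted for baseline, or the group-by-time term. The baseline-adjusted form is safer, since it does not lose power when the baseline correlation is low. State that within-arm and baseline comparisons are descriptive and lie outside the Bonferroni family of that contrast. This restores the alpha on which the trial was sized.

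If the treatment contrast is to stay in the family, state the number of comparisons and replace the 80% in Sample size with the matching power, for example about 62% for four or 56% for six.

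Decide separately whether to control multiplicity across the three primary outcomes. If Bonferroni over three is adopted, state its cost: about 66% power at 26 per arm without baseline adjustment, or about 78 participants for 80%.

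The wording change needs no new data. Its downside is that within-arm comparisons lose their confirmatory p-values.
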